### Informed consent

Study staff will explain the nature of the study to the most senior member of the household present, and who is aged 18 years or more, in a language understandable to her/him, and answer any questions they have about the study. The study staff will leave an informed consent form along with the other study materials. During the telephone call to report results, the participant will be verbally asked if they consent to participate in this study. The 120 people who will be surveyed in the face-to-face interviews will also be given the opportunity to provide informed consent.

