## Methods/design

### Design

This is a parallel group, non-blinded, cluster randomised superiority trial comparing the secondary distribution of HCV self-tests with the secondary distribution of information pamphlets encouraging individuals to visit a testing facility for HCV screening. A subset of participants (*n* = 120) from both the intervention and control groups will be asked to participate in face-to-face interviews regarding their perceptions of the testing experience, to provide insights into the acceptability and feasibility of HCV self-testing. The study timeline is shown in Table 1.

**Table 1 Tab1:** Study timeline

	**Enrolment**	**Follow-up for all participants**	**Follow-up for HCV antibody-positive participants**
**Procedure**	**Day 1**	**Months 1–2**	**Months 1–8**
Inclusion and exclusion criteria	X		
Informed consent obtained	X		
HCV antibody testing (either HCV self-test left with the household or participants in the control group attend Memon Goth Hospital)	X	X	
Collection of test results and survey of perceptions of the testing process		X	
Referral of HCV antibody-positive individuals for confirmatory testing and linkage to care		X	X
Linking of data for the RDT (control group) and RNA test and treatment initiation (as applicable for the intervention and control groups)		X	X
Adverse event (AE)/serious adverse event (SAE) review	X	X	X
Cost data collection and analysis	X	X	X

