### Eligibility criteria

Participants are only eligible to be included in the trial if they meet all of the following inclusion criteria: ≥ 18 years of ageResiding in UC9 or 10Not yet reached for testing as part of the larger micro-elimination programmeNot known to be HCV antibody-positiveNot tested for HCV within the past 6 monthsEligible for inclusion in the larger micro-elimination programme

Participants will be excluded from the trial if they are at home on the day that AKU study staff visit to either leave an HCV self-test or the information materials encouraging those who were previously missed to attend for facility-based HCV testing.

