**Fig. 3 Fig3:**
[figure not shown]
Trial flow diagram

In the control group, if the participant(s) are not at home, the study staff will leave information about HCV testing and direct them to the nearest clinic that offers HCV testing services; the participant(s) will not be left an HCV self-test. Study staff will however leave a mobile phone number for the participant(s) to call if they need further information on HCV testing.

In both groups, if no-one is at home or no one aged 18 years or more is present, the study staff will make as many return visits as necessary to contact a household member.

A small incentive, comprising a 500 rupee (approximately 3 USD) phone credit voucher, will be provided to participants in both the intervention and control groups for any information they return via a phone call, including whether they took the test and, if so, what the result was. During this return phone call, the study team will follow up with the participant to inquire whether they completed the test, record any test results, and conduct a brief interview.

For all participants who report a positive HCV antibody test, study staff will make an appointment to return to their house to enrol them in the larger micro-elimination programme. During this home visit, they will complete a blood draw for HCV viraemia testing and APRI (aspartate aminotransferase to platelet ratio index) liver staging, to be performed at Memon Goth Hospital. The viraemia testing will be performed using an HCV core antigen assay (ARCHITECT HCV Ag assay, Abbott® Diagnostics). If a participant’s result is in the grey zone (≥ 3 to ≤ 10 fmol), a second sample from the same participant will be tested for HCV RNA (Xpert HCV Viral Load, GeneXpert® IV, Cepheid, France) to determine viraemia. If the participant is viraemic, further care and treatment will be provided to their doorstep. All participants who report a negative HCV antibody test will be encouraged to seek a retest, as per the national guidance.

Approximately 1 month following the start of enrolment, face-to-face interviews will be conducted with a subset of participants in both the intervention and control groups, to explore their perceptions of the testing process.

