### Statistical methods

The data will be analysed using R version 4.1 or higher. A summary of statistical analyses that will be completed by the endpoint is shown in Table 2. The primary analysis will be performed using an intention-to-test analysis. The incentivisation methods described above will be employed to minimise missing data. The complete analysis plan is described in the study statistical analysis plan, which was drafted at the time the protocol was developed.

**Table 2 Tab2:** Statistical analyses to be completed by the endpoint

**Endpoint**	**Statistical analysis method**
1.1 The number and estimate of the proportion of participants who report completing HCV antibody testing in the intervention group 1.2 To assess whether the proportion of participants who report completing HCV antibody testing in the intervention group is greater than that of participants in the control group, by a margin of 20%	Test of proportions, comparing the proportion of individuals reporting HCV test results in the intervention versus control groups and between intervention groups
2.1 The number and estimate of the proportion of HCV antibody-positive individuals made aware of their status in the intervention versus the control group	Descriptive statistics; statistical tests comparing the number of individuals in the intervention versus the control group and between intervention groups
2.2 The number and estimate of the proportion of HCV antibody-positive individuals who are referred to and complete HCV RNA confirmatory testing in the intervention versus the control group	
2.3 The number and estimate of the proportion of HCV RNA-positive individuals who begin treatment in the intervention versus the control group	
2.4 Analysis of survey responses using proportions and means	Descriptive statistics for survey responses (e.g. proportions, means)
2.5 Cost per test completed and cost per person diagnosed (serology, RNA) in the intervention versus the control group	Ingredients-based cost calculation approach

The estimates of the study outcomes are proportions pfo,X, (fo = favourable outcome, X = element of {intervention, control}). They will be based on the definitions shown in Table 3, for estimation as well as for between-arm comparison.

**Table 3 Tab3:** Analysis table for primary and secondary analyses

Outcome							
		Favourable; test completed				Non-favourable; test not completed	Total

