### Limitations

This study has some important limitations that will be considered and described in the study report. The uptake of testing in the control arm may be affected by the geographical location of the participant and the distance to Memon Goth Hospital, as well as by the ongoing COVID-19 pandemic, which may affect participants’ willingness to visit a healthcare facility. The interview questionnaires have a multiple-choice design, which may not capture some important context-specific aspects.

Cluster randomised trials have the possibility of cross-contamination bias; however, in this study the risk of cross-contamination bias is limited, because the control group will not have access to HCV self-tests as they are not currently on the market in Pakistan. Given that the time between enrolment and result return is expected to take up to a maximum of 1 month, incentives are offered for the return of results, and “did not complete the test” is an option for the return of the results; therefore we are not anticipating a large attrition bias. Detection bias will be minimised by clearly defining the study procedures used to measure the outcomes and by using the same procedures and data collection tools in both the intervention and control groups, for example the result reporting procedure is the same across both the intervention and control groups, with the same data collection tool, result reporting procedure, and result reporting timeframe.

The WHO HCV self-testing guidelines recommend that HCV self-testing delivery models, support tools and referral pathways are designed and adapted according to the local context and community preferences. This study will provide an opportunity to pilot implementation approaches and explore their feasibility in the context of micro-elimination efforts. These approaches can be refined and optimised for broader use in national testing plans, based on the lessons learned. Given the significant burden of HCV in Pakistan and elsewhere, this study will inform efforts to scale-up approaches to diagnose individuals with HCV who would otherwise not access testing and link them to effective treatment. Further studies can be conducted to assess other implementation models in different settings.

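### The absent person's consent and the primary outcome come from the same phone call after randomisation, and the article leaves open whether non-responders count in the primary denominator

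*Protocol article*

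**What the plan says.** All references are to the protocol article.

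- **Informed consent.** Staff explain the study to the most senior adult present. "The study staff will leave an informed consent form along with the other study materials". The absent person is asked later: "During the telephone call to report results, the participant will be verbally asked if they consent to participate in this study". No other place describes that person's own consent to the trial. The only other consent step is for the face-to-face interviews.
- **Design, Table 1.** The row "Informed consent obtained" is ticked under Enrolment, Day 1. Collection of results is in Months 1–2.
- **Eligibility criteria.** "Participants will be excluded from the trial if they are at home on the day that AKU study staff visit". Consent is not among the inclusion criteria.
- **Trial processes and intervention.** A voucher is paid in both arms "for any information they return via a phone call, including whether they took the test and, if so, what the result was".
- **Statistical methods.** "The primary analysis will be performed using an intention-to-test analysis". The term is not defined further. The next sentence relies on the incentives to keep missing data low. Table 3 divides completed tests (a to d, f to i) by completed plus not completed (adding e and j).
- **Limitations.** Little attrition bias is expected, partly because not having completed the test "is an option for the return of the results".

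**The concern.** A participant is absent on Day 1 by definition, so cannot give consent in person on the day Table 1 shows it. The consent that the text does describe falls in the call that yields the primary outcome. That call comes after allocation, and after an unblinded delivery of either a kit or a pamphlet.

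Someone who is never reached by phone gives neither consent nor an outcome, and someone who declines in the call gives no consent. The article does not say whether such people are counted in cells e and j or leave the denominator.

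If they leave, the comparison is between groups formed after randomisation by willingness to respond. Responding may well depend on having tested, and may differ by arm, because one arm has a kit at home and the other needs a hospital visit. The primary test is against a 20-point margin, so the choice of denominator could decide the trial.

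**Working it through.** **1. The text.** Three statements cannot all hold for one person: consent on Day 1 (Table 1), absence on Day 1 (Eligibility criteria), and consent asked in the results call (Informed consent).

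On the denominator, the article points both ways:

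- *Everyone approached:* the intention-to-test label, the not-completed cell in each denominator, Enrolment on Day 1 in Table 1, and the reference in Limitations to a period running from enrolment to result return.
- *Responders only:* an unreturned result is described as missing data (Statistical methods) or attrition (Limitations). If non-responders were simply counted in e and j, failure to call would cause neither in the primary outcome. Limitations also presents non-completion as an answer given when results are returned.

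The no-result cells d and i sit in the numerator, under completed tests, so they are not the place for non-responders.

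**2. Size.** The article gives no testing, response or dropout rate, so there is no figure of the plan's own to reproduce. All rates below are assumptions.

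Let p be the proportion who tested, r1 the response rate among testers and r0 the response rate among non-testers.

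- All approached, non-responders counted as not completed: p × r1
- Responders only: p × r1 / [p × r1 + (1 − p) × r0]

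With r1 = 90% in both arms (each pair is intervention / control):

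| p | r0 | All approached | Responders only |
|---|---|---|---|
| 50% / 30% | 90% / 90% | 45 − 27 = 18.0 | 50.0 − 30.0 = 20.0 |
| 50% / 30% | 10% / 10% | 18.0 | 90.0 − 79.4 = 10.6 |
| 50% / 30% | 20% / 50% | 18.0 | 81.8 − 43.5 = 38.3 |
| 50% / 30% | 50% / 20% | 18.0 | 64.3 − 65.9 = −1.6 |
| 30% / 30% | 30% / 60% | 27 − 27 = 0.0 | 56.25 − 39.13 = 17.1 |
| 30% / 30% | 60% / 30% | 0.0 | 39.13 − 56.25 = −17.1 |

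Third row in full. Intervention: 0.50 × 0.90 = 0.45 and 0.50 × 0.20 = 0.10, so 0.45/0.55 = 0.818. Control: 0.30 × 0.90 = 0.27 and 0.70 × 0.50 = 0.35, so 0.27/0.62 = 0.435. The difference is 0.383.

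The same effect in counts, with 1,000 people approached per arm:

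- 650 of 700 responders tested (intervention) and 400 of 450 (control): 650/1000 − 400/1000 = 25 points, against 650/700 − 400/450 = 4.0 points.
- 750 of 800 and 250 of 300: 750/1000 − 250/1000 = 50 points, against 750/800 − 250/300 = 10.4 points.

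**3. Against the margin.** In both count examples the estimate among all approached lies above 20 points and the responders-only estimate lies below, where the test cannot succeed. In the third table row the true difference is exactly 20 points, which belongs to the null hypothesis, yet responders only shows 38.3. The error can therefore hide an effect or create one.

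**The case against.** A reader might infer that the plan analyses callers only. The document does not support that. Consent is not an inclusion criterion. The Sample size section enrols people who meet the inclusion criteria. Trial processes already calls absent people participants at the visit, and Limitations places enrolment before result return. With the intention-to-test label and the not-completed cell, everyone approached is the more natural reading. This stands: responders only is a permitted reading, not the stated plan.

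A reader might also infer that reported completion among responders would be close to 100% in both arms. That is unsupported too. The voucher pays equally for saying that no test was done, and the interview plan provides for up to 15 non-completers in each of four subgroups (4 × 15 = 60), so the trial expects to hear from non-testers. With equal responding the bias disappears (first table row).

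Nor does the article say that results calls are inbound only. It also has the study team following up with the participant. The point does not depend on who dials, because a person who is not reached still gives neither consent nor outcome.

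Finally, handling of non-responders commonly belongs in the statistical analysis plan, which is said to exist and is not shown. That is fair for the definition of the analysis set. It does not cover the timing of consent, or whether people who were never asked, or who declined, may be counted. Those are protocol and ethics matters, and the protocol states the timing inconsistently.

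**Conclusion.** The concern holds in limited form. The conflict between Table 1, the Eligibility criteria and the Informed consent section is plain and must be reconciled. Because individual consent is tied to the call that supplies the primary outcome, and unreturned results are described as missing or attrition, the intention-to-test denominator has two tenable readings.

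Only the reading that includes everyone approached keeps the randomised comparison. The other can shift the difference in either direction: by 17.1 points with no true effect, and from 18.0 to 38.3 or −1.6 points with a true 20-point effect. Those sizes rest entirely on assumed testing and response rates. They show that the choice can change the conclusion against the margin, not that it will. The harm requires responding to depend on test status; the largest shifts arise when that dependence also differs by arm.

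**What to change.** 1. Correct the consent row of Table 1 so that it agrees with the Informed consent section.
2. Define the primary denominator, in both arms, as every eligible absent adult for whom a kit or pamphlet was left, recorded per person at the visit. Kits are already left one per missed person. Control households need an equivalent pamphlet count.
3. Count anyone with no returned result by the end of a fixed window, or who declines in the call, as not completed in both arms. Use anonymous counts, with ethics committee agreement. Fix the window: Table 1 allows Months 1–2, whereas Limitations expects at most 1 month.
4. Report response rates by arm, with a responders-only analysis as a sensitivity analysis.
5. Table 1 plans to link hospital rapid-test data for the control group. Any use of these records to reclassify control non-responders as tested should be secondary only, labelled as one-sided against the intervention (self-testers who do not report have no such record), and subject to ethics approval, since it needs identifiable data on people who have not consented.

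**Cost.** Protocol wording, an ethics submission and a per-person visit log in the control arm. Known antibody status and testing in the past 6 months may not be on the programme's list of missed people, so how they are established at the visit must be the same in both arms. The main statistical downside is that people who tested but did not report count as not completed. In the first table row this turns a true 20 points into 18.0.

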### Trial processes and intervention

The neighbourhoods in UCs 9 and 10 will be grouped into clusters. These clusters will be matched in terms of similarity of geography (peri-urban or rural), population size, and age demographics. Each member of a matched cluster pair will be randomised to the intervention or control groups.

As outlined in Fig. 3, AKU study staff will return to the households where individuals were missed during the first round of house-to-house screening carried out as part of the larger micro-elimination programme. In the intervention group, the study staff will leave as many HCV self-tests as there were individuals missed from the first round of house-to-house screening who are still not present during the visit, as well as instructions for use, with the most senior member of the household present. The study team will also explain the HCV self-testing process, using a standardised explanatory checklist, to that same senior member of the household; they will also leave a mobile phone number for the participant to call if they need help in conducting the test. Participants will be provided with various types of support to minimise the occurrence of errors during the self-testing process and any possible confusion in interpretation of the test results. Printed instructions for use in Urdu will be delivered with the test kits, which will also contain pictorial guides on how to use the test. Participants will have access to a live chat facility and a call centre.

**Fig. 3 Fig3:**
[figure not shown]
Trial flow diagram

In the control group, if the participant(s) are not at home, the study staff will leave information about HCV testing and direct them to the nearest clinic that offers HCV testing services; the participant(s) will not be left an HCV self-test. Study staff will however leave a mobile phone number for the participant(s) to call if they need further information on HCV testing.

In both groups, if no-one is at home or no one aged 18 years or more is present, the study staff will make as many return visits as necessary to contact a household member.

A small incentive, comprising a 500 rupee (approximately 3 USD) phone credit voucher, will be provided to participants in both the intervention and control groups for any information they return via a phone call, including whether they took the test and, if so, what the result was. During this return phone call, the study team will follow up with the participant to inquire whether they completed the test, record any test results, and conduct a brief interview.

For all participants who report a positive HCV antibody test, study staff will make an appointment to return to their house to enrol them in the larger micro-elimination programme. During this home visit, they will complete a blood draw for HCV viraemia testing and APRI (aspartate aminotransferase to platelet ratio index) liver staging, to be performed at Memon Goth Hospital. The viraemia testing will be performed using an HCV core antigen assay (ARCHITECT HCV Ag assay, Abbott® Diagnostics). If a participant’s result is in the grey zone (≥ 3 to ≤ 10 fmol), a second sample from the same participant will be tested for HCV RNA (Xpert HCV Viral Load, GeneXpert® IV, Cepheid, France) to determine viraemia. If the participant is viraemic, further care and treatment will be provided to their doorstep. All participants who report a negative HCV antibody test will be encouraged to seek a retest, as per the national guidance.

Approximately 1 month following the start of enrolment, face-to-face interviews will be conducted with a subset of participants in both the intervention and control groups, to explore their perceptions of the testing process.

As this study is intended to measure whether there is an increase in testing following the secondary distribution of HCV self-testing compared with the standard of care facility-based testing, facility-based testing was chosen as the comparator. In both groups, if a previously missed individual is at home when a study staff member visits, they will enrol the person in the larger micro-elimination programme (and not this study).

### Strategies to increase recruitment

As part of the larger micro-elimination programme, AKU has already established a community oversight board comprising community leaders from neighbourhoods UC 9 and 10. This community oversight board has been informed about this new study component. AKU works with the community oversight board to sensitise each neighbourhood to the study, to facilitate information sharing and encourage interest in participating in the study.

### Outcomes

The primary outcome is to assess whether the proportion of participants who report completing HCV antibody testing in the intervention group is greater than that of the participants in the control group by a margin of 20%.

The secondary outcome measures are as follows.The number and estimate of the proportion of HCV antibody-positive individuals made aware of their antibody status in the intervention versus the control groupThe number and estimate of the proportion of HCV antibody-positive individuals who are referred for and complete HCV RNA confirmatory testing in the intervention versus the control groupThe number and estimate of the proportion of HCV RNA-positive individuals who begin treatment in the intervention versus the control groupThe cost per test completed and the cost per person diagnosed (serology, RNA) in the intervention versus the control groupAn analysis of the knowledge, attitudes and practice survey responses will be conducted, using proportions and means

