**Methods:**

This is a parallel group, non-blinded, cluster randomised trial comparing secondary distribution of HCV self-testing with secondary distribution of information pamphlets encouraging individuals to visit a testing facility for HCV screening. The cluster allocation ratio is 1:1. Clusters will be randomised either to HCV self-testing distributed via study staff or control clusters where information on HCV will be given and the participant will be requested to attend their local hospital for HCV screening. In both clusters, only households with a member who has not yet been screened as part of the larger micro-elimination project will be included. The primary outcome is the number and proportion of participants who report completion of testing. Secondary outcomes include the number and proportion of participants who a) receive a positive result and are made aware of their status, b) are referred to and complete HCV RNA confirmatory testing, and c) start treatment. Acceptability, feasibility, attitudes towards HCV testing, and cost will also be evaluated. The target sample size is 2,000 participants.

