**Fig. 2 Fig2:**
[figure not shown]
Map of UC10. Maps created using Adobe Illustrator 25.4 for Windows. https://www.adobe.com/ro/products/illustrator.html?skwcid=AL!3085!3!341240180390!e!!g!!adobe%20illustrator&mv=search&sdid=KCJMVLF6&ef_id=CjwKCAiAgbiQBhAHEiwAuQ6Bknh2k612ZgbuSDwblwUKE5L1T1KaZATGaxTwAGIkknQrdcWhGZ6JrxoCtNAQAvD_BwE:G:s&s_kwcid=AL!3085!3!341240180390!e!!g!!adobe%20illustrator!1478481991!58339249918&gclid=CjwKCAiAgbiQBhAHEiwAuQ6Bknh2k612ZgbuSDwblwUKE5L1T1KaZATGaxTwAGIkknQrdcWhGZ6JrxoCtNAQAvD_BwE

Participants in the control clusters will be directed to Memon Goth Hospital for facility-based HCV testing; if a participant tests positive by HCV rapid diagnostic test (RDT), they will immediately have blood drawn for viraemia testing. As described below, for those in the self-test group who report a positive self-test, a member of the AKU team will come to their house to perform a blood draw for viraemia testing and liver staging. Treatment for both groups will be provided at each participant’s doorstep, free of charge, through a partnership between AKU and The Liver Foundation.

As there is currently no quality-assured HCV self-test available, the professional-use OraQuick® HCV Rapid Antibody Test, which has been adapted by the manufacturer for self-testing by being repackaged and labelled with instructions for use, will be used in this trial. The OraQuick® HCV Rapid Antibody Test is prequalified by WHO and CE-marked for professional use (sensitivity 98.1%, specificity 99.6%). The OraQuick® HCV Self-Test kits provided to participants in the intervention group will be labelled for Research Use Only (RUO).

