### Participant timeline

#### Sample size

A minimum of 2,000 participants who meet the inclusion criteria will be enrolled in the study. There will be up to 20 clusters, each comprising up to 150 to 200 households: 5 intervention clusters each in rural and peri-urban areas and 5 control clusters each in rural and peri-urban areas. The study is powered to detect at least a 20% between-group difference in HCV antibody self-testing, based on 80% statistical power and an alpha level of 0.05.

The survey of participants’ perceptions in relation to testing will include face-to-face interviews with 60 participants from each of the intervention and control groups. This is guided by empirical thinking, considering the feasibility with regards to the time and staff required to conduct the in-person interviews. The aim of these interviews is to further expand our understanding of preferences around HCV self-testing; there is no intention to set specific targets for measurement.

For the primary objective, the null hypothesis is that there is no significant difference in the proportion of individuals reporting HCV test results in the intervention versus control groups. The alternative hypothesis is that home delivery of HCV self-tests will significantly increase the proportion of individuals reporting HCV test results.

The study is not powered to detect significant differences in the secondary objectives. However, similar to the primary objective, the null hypothesis would be no significant difference between the intervention versus control groups. The alternative hypothesis would that home delivery of HCV self-tests will result in significantly higher numbers of HCV-infected individuals being diagnosed, linked to care and treated, making it a cost-effective approach to HCV case finding and elimination.

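### Secondary endpoints 2.1 to 2.3 are stated as proportions of people found positive in one place and of participants in another; the first form is uninformative for 2.1 and not a randomised comparison for 2.2 and 2.3

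*Protocol article*

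**What the plan says.** The Protocol article gives two denominators for the same endpoints.

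- **Outcomes and Table 2 (Statistical methods).** Endpoint 2.1 is the "proportion of HCV antibody-positive individuals made aware of their antibody status". Endpoint 2.2 is the "proportion of HCV antibody-positive individuals who are referred for and complete HCV RNA confirmatory testing". Endpoint 2.3 is the "proportion of HCV RNA-positive individuals who begin treatment in the intervention versus the control group". Study aim and objectives words linkage and treatment in the same conditional way.
- **Abstract, Methods.** "Secondary outcomes include the number and proportion of participants who a) receive a positive result and are made aware of their status", followed by confirmatory testing and treatment start on the same base of participants.

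Of the outcome proportions, Statistical methods says: "They will be based on the definitions shown in Table 3, for estimation as well as for between-arm comparison". Table 3 places positive results only under completed tests. Formulas with the whole arm as denominator are written out for the primary outcome only.

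Each of 2.1 to 2.3 also reports a number, and Table 2 says the between-arm tests compare numbers of individuals. The Sample size section says the secondary objectives are not powered and states their alternative hypothesis as "significantly higher numbers of HCV-infected individuals being diagnosed, linked to care and treated".

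**The concern.** Antibody status is learned only by taking the test that the trial is trying to promote; no independent serosurvey is described. A proportion among known positives therefore starts after the step that self-testing is meant to change.

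For 2.1, nearly everyone who can be counted as positive has already been made aware. For 2.2 and 2.3, the denominator is formed after randomisation by who tested. People who travel to a hospital and people who use a kit left at home may differ in ways that also affect follow-through, so the comparison no longer has the protection of randomisation.

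What is at stake is how the secondary results are read. The stated hypothesis is about more people diagnosed, linked and treated. A conditional proportion does not measure that, and could show self-testing as worse in a trial where it brought more people to confirmation and treatment.

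**Working it through.** The plan states no figure for these endpoints, so there is none to reproduce.

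**Step 1. What Table 3 makes available.** Positives are cells a and b (intervention) and f and g (control). Non-completers, e and j, carry no antibody status, and completers without a result, d and i, are not positives. The only antibody-positive denominators are thus a+b and f+g.

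- Proportion 2.1 becomes about (a+b)/(a+b) versus (f+g)/(f+g), that is, about 100% versus 100%. It is near rather than exactly 100%, because Table 1 plans linkage of control rapid-test data, so a recorded control positive who never learned the result is conceivable.
- Proportion 2.2 is conditional on a+b and f+g. Proportion 2.3 is conditional on a further subset, for which Table 3 has no column.

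**Step 2. Can the conditional and per-participant comparisons disagree?** Inputs:

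- N = 1,000 per arm (minimum 2,000, allocation 1:1).
- Prevalence 5% (Background). This is the share living with HCV, used here as a stand-in for antibody prevalence: an assumption.
- Sensitivity 98.1% (Study setting, professional use).
- Uptake U and completion of viraemia testing among known positives C: not in the document, assumed. Uptake pairs are set 20 points apart, as in the Sample size section.

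Known positives = N × 0.05 × U × 0.981. Completions = known positives × C.

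At U = 30% (control) and 50% (intervention): 1,000 × 0.05 × 0.30 × 0.981 = 14.7 and 1,000 × 0.05 × 0.50 × 0.981 = 24.5. Per participant, endpoint 2.1 is then 1.5% versus 2.5%, against about 100% versus 100% conditionally.

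| Uptake, control / intervention | C, control / intervention | Conditional difference (intervention − control) | Completions per 1,000, control / intervention |
|---|---|---|---|
| 30% / 50% | 100% / 80% | −20 points | 14.7 / 19.6 |
| 40% / 60% | 100% / 80% | −20 points | 19.6 / 23.5 |
| 60% / 80% | 100% / 80% | −20 points | 29.4 / 31.4 |
| 60% / 80% | 100% / 70% | −30 points | 29.4 / 27.5 |

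In the first three rows the signs are opposite; in the last both favour control.

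**Step 3. General condition.** With equal prevalence and test accuracy in both arms, these cancel. The signs oppose when

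U(control)/U(intervention) < C(intervention)/C(control) < 1.

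The lower bound is 30/50 = 0.60, 40/60 = 0.67 and 60/80 = 0.75 for the three uptake pairs. Over a grid of 12 scenarios with lower completion in the intervention arm, 11 showed opposite signs. The grid was chosen by hand, so this is not a probability.

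**Step 4. Are the counts enough?** Suppose 1,100 eligible adults in one arm and 900 in the other, with 2% diagnosed in each (assumed). The counts are 1,100 × 0.02 = 22 and 900 × 0.02 = 18: a difference with no effect behind it. The allocation section names population size among the matching factors, but its working rule pairs clusters on average household size, so equal numbers of eligible adults are not assured.

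**Step 5. Precision after the change.** For 1.47% versus 1.96%, the standard error ignoring clustering is √(0.0147 × 0.9853/1,000 + 0.0196 × 0.9804/1,000) = 0.0058. The difference of 0.49 points has a 95% interval of about −0.6 to 1.6 points, and clustering would normally widen it.

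**The case against.** The strongest reply is that the plan does not rest on the conditional proportions alone. Every one of 2.1 to 2.3 reports a number, Table 2 says the tests compare numbers, and the secondary hypothesis is about numbers. In the first row of the table above, 19.6 versus 14.7 would be visible to any reader. The Abstract already uses participants, and a separate analysis plan, not shown, may fix the denominators. Conditional cascade steps also answer the objectives as worded. All of this stands and limits the harm. It does not make the stated proportions informative between arms, it does not settle which of two denominators applies, and counts without a denominator depend on arm size.

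Three stronger readings are tempting and are not supported.

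- *That the secondary results will come out reversed.* The document gives neither uptake nor completion by arm, so reversal is a possibility only.
- *That slower confirmation in the self-test arm is established.* Study setting says of control participants with a positive rapid test that "they will immediately have blood drawn for viraemia testing", with a home visit for self-test positives. Trial processes and intervention instead describes a home appointment and blood draw for everyone who reports a positive test. The two accounts of the control pathway conflict, so neither can carry an argument about arm differences.
- *That 2.2 and 2.3 literally cover only a small minority.* Trial processes and intervention says: "The viraemia testing will be performed using an HCV core antigen assay", with RNA reserved for grey-zone results. The wording mismatch is real, but no grey-zone frequency is given, and the RNA wording is plausibly shorthand for viraemia testing.

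**Conclusion.** The concern holds in a limited form. The document states two denominators for the same endpoints. Under the one in Outcomes and Table 2, read with Table 3, proportion 2.1 is near 100% in both arms by construction, and proportions 2.2 and 2.3 compare subsets selected after randomisation. The first conclusion needs only that untested people have no known status. Disagreement in sign with the per-participant effect needs lower completion in the intervention arm, within the range in Step 3, and rests on assumed rates.

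The planned counts soften the consequence. These endpoints are secondary and unpowered, and the primary conclusion is unaffected. The change is worth making because it is cheap and brings the between-arm comparison into line with the stated hypothesis.

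**What to change.** - For between-arm comparison of 2.1 to 2.3, use all eligible participants in each arm's randomised clusters as the denominator: a+b+c+d+e and f+g+h+i+j in Table 3. Compare with a method that accounts for clustering.
- Keep the proportions among antibody-positive and viraemic people as descriptive cascade steps within each arm, without a test.
- Align the Abstract, Study aim and objectives, Outcomes, Table 2 and Table 3 on this.
- Align the HCV RNA wording of 2.2 and 2.3 with the viraemia testing described under Trial processes and intervention (core antigen, with RNA for grey-zone results).
- Reconcile Study setting with Trial processes and intervention on how control positives reach viraemia testing.

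The same data serve. The costs are small percentages with wide intervals, few events per cluster (about 15 to 25 known positives per arm over up to 10 clusters in the 30% versus 50% case), which makes any clustered test fragile, and a documented amendment, since enrolment began in November 2021.
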